The cancer survival rate is increasing, raising the need to create high-quality survivorship care plans. Often, follow-up of cancer survivors does not fully address behavioral and psychosocial elements that could improve the quality of life of these patients and decrease the risk of recurrence. Currently, there is a lack of brief, validated tools to assess diet, lifestyle, and other behaviors that could influence quality of life and prognosis in cancer survivors. The hypothesis of this project is that the creation of a screener with the capacity to quickly, validly and effectively evaluate nutritional factors, lifestyle, sleep quality and the psychosocial dimension in cancer survivors could be useful in identifying people who may need further care and support. The aim is to create a valid and rapid tool (Life S-Can) to assess a total of seven dimensions (body composition, physical activity, diet, alcohol intake, smoking, sleep behavior and psychosocial factors) in cancer survivors for use in a clinical setting to improve survivorship care and quality of life. The project is divided into four phases and will be carried out at the Son Espases University Hospital (HUSE) (Palma). The objective of Phase I is to design the Life S-Can questionnaire in English together with an international and multidisciplinary panel of experts in cancer, nutrition, epidemiology, primary care, psychology and psychometrics. This first version will be administered to a small convenience sample (n=20) to determine understandability, clarity, and usefulness. In Phase II, Life S-Can will be validated in a total of 100 cancer survivors at HUSE. To do this, patients will be recruited by the Oncology Department and will be invited to go to the Clinical Trials Unit for a comprehensive evaluation. A dietitian will administer Life S-Can and then collect data using validated assessment methods (using validated questionnaires and objective measurements) to compare with data obtained with the Life S-Can. Phase III consists of a pilot intervention study, where participants recruited in Phase II will be randomized to the intervention group or control group. Participants in the intervention group will be offered visits with a health professional (dietitian, physical activity and/or psychology), based on their responses to the Life S-Can, who will provide advice over 3 months. Phase IV is a qualitative study conducted in cancer patients and healthcare professionals (n=40) to obtain data to future design a complex intervention to test the feasibility and effectiveness of implementing Life S-Can in a clinical setting. The care of cancer survivors must be multifactorial; however, often, due to time constraints and clinical burden, healthcare professionals may not adequately assess certain aspects relevant to the quality of life of cancer survivors, such as nutritional status, diet and physical and mental health. Life S-Can will enable doctors, healthcare professionals, charities and other stakeholders to work with cancer survivors from the outset and refer them to appropriate mental health and care teams and resources.

1. **Background and state of the art**

The number of cancer survivors is increasing substantially, mainly due to an ageing population and advances in screening programs and treatments^1,2,3^. Traditionally, follow-up of cancer survivors has focused on detection of cancer recurrence or new cancers, but often it does not fully address behavioral and psychosocial elements which could improve quality of life (QoL) and decrease recurrence risk^4^, and thus may miss important survivor concerns and needs^5^. Therefore, implementing more effective models of care which support patients and detect their needs or after-effects is key in future survivorship care plans^4^. In terms of nutritional and lifestyle factors (body weight, physical activity, diet and alcohol intake), the WCRF/AICR state that, although evidence is still not strong enough to make specific recommendations, cancer survivors should follow cancer prevention guidelines^1^. Furthermore, studies show that cancer survivors often report poor sleep quality and can suffer from varying degrees of psychosocial distress and mental health issues^6,7,8,9,10^.

The Principal Investigator (PI), together with her supervisor, recently developed a short screener to assess adherence to the 2018 WCRF/AICR recommendations for cancer prevention (ongoing); however, it only contemplates body weight, physical activity, diet, alcohol and breastfeeding, and does not consider other dimensions relevant for cancer survivor’s QoL, such as other consideration of body composition beyond obesity (for example sarcopenia, which is highly prevalent in cancer patients and survivors^11^), sleep quality or psychosocial distress. It has been previously suggested that survivorship care guidelines should include screening for common problems and address general survivorship issues^12^, as well as consider further endpoints other than cancer recurrence, such as improvement of health-related behaviors and overall QoL^9^. Efforts have been made towards this objective^13^; however, there is still a lack of short, validated screeners to assess diet, lifestyle, physical health (sarcopenia) and mental and psychosocial concerns as a whole for cancer survivors, which reflect current recommendations for this population and undertake a more multidisciplinary, holistic health-care approach. Thus, a validated and rapid tool which could effectively operationalize all these factors and determine adherence to current guidelines with the ability to identify individual needs, could improve survivorship care and individual risk prediction. Similar tools have been shown to be useful for other conditions, such as Life’s Essential 8^14^, by assisting individual patients and health care teams in cardiovascular health assessment and progress tracking.

Thus, the overall goal of this proposal is to develop and validate a screener (Life S-Can) based on the current dietary and lifestyle recommendations for cancer survivors, as well as to carry out a qualitative study to help design a complex intervention in the future to test the feasibility and effectiveness of implementation of Life S-Can in clinical settings. This tool would enable clinicians work together with cancer survivors early-on, which often need continued support after surviving a cancer, and screen those patients who may need referral to other health and mental care teams and resources. Such a tool could improve survivorship care, QoL and may decrease recurrence risk.

1. **References**

The increasing number of cancer survivors worldwide, and the evident continued health and mental care support they often require once they have finished treatment, highlights the current lack of short, validated screening tools to determine diet, lifestyle, sleep behaviour and psychosocial distress in this population. The group with whom the PI of the project pertains to has previously developed a short screener to evaluate adherence to the 2018 WCRF/AICR cancer prevention recommendations, which has given the PI in-depth experience in the development and validation of such tools.

**The aim of this project is to develop a valid and rapid screening tool (Life S-Can) with the capacity to evaluate a total of seven domains (body composition, physical activity, diet, alcohol intake, smoking, sleeping behaviour and psychosocial distress) in cancer survivors for its use in a clinical setting to improve survivorship care and QoL.** The project is divided into four specific aims (SA) and will be carried out in one year at the University Hospital Son Espases (HUSE) (Palma, Spain).

**SA1: Develop a short screener (Life S-Can) to evaluate body composition, physical activity, diet, alcohol intake, smoking habits, sleeping behaviour and psychosocial distress in cancer survivors**.

- A1.1. Organize an online international, multidisciplinary expert panel in oncology, nutrition, primary care, psychology, psychometry and epidemiology.
- A1.2. Design the screener in English together with the expert panel: number of questions per domain, instructions needed, examples given and scoring system will be agreed upon.
- A1.3. Translate the screener to Spanish (translation/back-translation method) and culturally adapt it to Spain with the collaboration of the listed Key Personnel.
- A1.4. Upload the screener onto specific software to create a user-friendly tool using external IT services.
- A1.5. Determine comprehension, clarity and usefulness of Life S-Can in cancer survivors using an adhoc questionnaire for the potential refinement of the tool.

**SA2. Determine relative and construct validity of individual domains and total score of the Life S-Can in cancer survivors using data obtained from validated and objective measurements.**

- A2.1. Recruit 100 cancer survivors from the Oncology Department at the HUSE.
- A2.2. Administer Life S-Can to all participants at the Clinical Trials Unit by a trained research dietitian. Re-administer after 7-10 days for reproducibility analysis (test-retest method).
- A2.3. Collect data of individual domains using validated questionnaires and objective measurements.
- A2.4. Data integration and statistical analysis to determine relative and construct validity of Life S-Can.

**SA3. Carry out a pilot intervention study in cancer survivors to determine the feasibility, acceptability and efficacy of Life S-Can.**

- A3.1. Recruit an expert panel in the field oncology specialised in diet, physical activity, lifestyle and cancer psychology, as well as cancer survivors (non-scientific actors).
- A3.2. Design a 3-month intervention plan with the expert panel and non-scientific actors, based on tailored sessions and personalized feedback according to Life S-Can answers, with the aim to improve QoL.
- A3.3. Randomize participants from A2.1. to either the intervention group (IG) or control group (CG). Offer a personalised intervention care plan to patients from the IG, based on their answers and score. Continue with standard care in patients assigned to CG.
- A3.4. Arrange appointments for IG patients at the Clinical Trial Unit with trained oncological dietitians, physical activity specialists and psychologists, depending on their answers (1 to 3 sessions, individual and as a group).
- A3.5. Re-administer Life S-Can and collect data on feasibility, acceptability and efficacy to all participants after 3 months since the first administration of Life S-Can (A2.2).
- A3.6. Data integration and analysis.

**SA4. Carry out a qualitative study in cancer survivors and health professionals to design a complex intervention to determine the feasibility and effectiveness of the implementation of Life S-Can in clinical settings.**

- A4.1. Design a qualitative study in a clinical setting (primary care, hospital) together with Key Personnel listed in the project.
- A4.2. Recruit 40 cancer survivors and health care professionals from the Oncology Department at the HUSE and in Primary Care clinics. Organize four focus groups and semi-structured like in-depth interviews (audio-recorded) of a duration of 1 hour.
- A4.3. Transcribe audios, collate data and analyze using thematic analysis.

1. **Type of study**

The project herein presented proposes four phases: tool development (Phase I); validation of the tool (Phase II - validation study); pilot intervention study (Phase III); and a qualitative study (Phase IV) to design a complex intervention in the future. All three phases and the type of studies carried out in each are described below. For this study to be successful, it will count of the participation of the following key personnel:

- [name], PI of the project and postdoctoral researcher of the NUTRECOR research group.
- [name], PI of NUTRECOR research group (IdISBa)
- NUTRECOR team (research dietitians)
- [name]
- [name]
- [name]
- [name]

1. **Materials and methods**

**PHASE 1. TOOL DEVELOPMENT:** The objective of phase I is to design the screener in an estimated period of three months (A1.1. to A.1.5).

**1. Organize an international, multidisciplinary panel of experts:** [name] will gather experts in cancer, nutrition, epidemiology, primary care, psychology and psychometry will be consulted. Local cancer patients’ organisations and charities will also be contacted throughout the project (based on previous collaborations).

**2. Design of screener:** The tool will include no more than 25 questions which cover a total of seven dimensions: body composition, physical activity, diet, alcohol consumption, smoking habits, sleeping behaviour and psychosocial distress (social support, stress, mental health) (Fig.2). The following considerations will be accounted for:

- Originally designed in English and translated to Spanish using the **translation/back-translation method**. Any subsequent changes in the screener will go through the same process ([name] & [name]).
- Questions will be designed in the most standardized manner as possible; however, if examples or additional instructions are necessary, they will be **culturally adapted** to the Spanish population (in a manner that they can be easily adapted to other cultures in the future).
- Possibility of being self-administered and/or administered by a health professional or researcher.
- Easy completion of screener and scoring system: Can be completed without specialised knowledge and scoring system easy to interpret to give **clinical decision support**.
- Upload the screener on an **adequate software** to complete using a phone, tablet or PC.

**3. Administer first version of Life S-Can to a small convenience sample (Study 1):** An n=10 of cancer survivors and n=10 health professionals/researchers (details on recruitment, inclusion and exclusion criteria described below) will be recruited by the Oncology Department of HUSE to complete the first version of Life S-Can, which will be administered by a research dietitian from the research group NUTRECOR. A short adhoc questionnaire will be prepared to administer to both participants and health professional/researchers involved to determine comprehension, clarity, usefulness of the tool, construct interpretation and acquiescence (apparent validity).

**PHASE II. VALIDATION STUDY:** It is expected that this phase will take an estimate of seven months to complete (based on the flow of cancer survivors at the hospital) (A2.1. to A2.4.).

**Study population:** Cancer survivors (n=100) will be recruited by the Oncology Department at the HUSE during routine follow-up visits to the hospital. The study aims to recruit survivors from most prevalent cancer types (i.e. breast, colorectal, lung); however, all cancer types will be considered. There is a lack of consensus regarding how to compute the sample size in validation studies, with recommendations ranging from 2 to 20 subjects per items and sample sizes ranging from 50 to 250 (*Anthoine E, Moret L, Regnault A, Sébille V, Hardouin JB. Sample size used to validate a scale: a review of publications on newly-developed patient reported outcomes measures. Health Qual Life Outcomes. 2014 Dec 9;12:176*). Thus, based on the literature, and assuming a 20% lost to follow-up, we will recruit 120 participants. This is a feasible number given the expected cancer survivors visiting the hospital in 1 year. **Inclusion criteria:** Adults ≥ 18 years old; men & women; able to read and understand Spanish; prior diagnosis of cancer (stages I to III); have completed all systemic treatment (surgery, chemotherapy, radiation therapy) at least ≥6 months prior to the study start date; be currently considered cancer free. **Exclusion criteria:** Ongoing cancer or cancer treatment; have a debilitating medical or psychiatric illness; presenting a disorder that compromises comprehension (e.g., dementia); pregnancy/breastfeeding.

[figure not shown]
If a participant agrees to participate, they will be given an information sheet (HIP_1), an informed consent (CI_1) and ten saliva collection tubes + instructions to take home. Once the participant has agreed to participate in the study, a research dietitian will contact the person to convene a day and time to meet at the Clinical Trials Unit. During this call, the dietitian will briefly explain what the study will entail and will give detailed instructions on how to collect saliva with the tubes previously administered (Salivette swabs for two days, at five different time points: at waking, 30 min after waking, at noon, at 5pm and anytime between 8-10pm).

**Workflow of the validation study (Study 2):** The validation study will consist into three visits to the research/hospital facility. The **first visit** will be at the Clinical Trials Unit, will take approximately 1 h and will be divided into three parts: 1) Administration of Life S-Can; 2) Administration of validated questionnaires; and 3) Obtain objective measurements of the patient. The **second visit** will also be at the Clinical Trials Unit and will take approximately 10-15 minutes. Participants will be asked to return the accelerometer and complete the Life S-Can questionnaire again (reproducibility). The **third visit** will be at the Nuclear Medicine Imaging Unit at the HUSE, for dual-energy x-ray absorptiometry (DXA) imaging. If possible, the second and third visit will be done on the same day, considering that the research facility is located within the hospital.

**1. Administration of Life S-Can to n=100 cancer survivors:** A research dietitian will collect standard sociodemographic and clinical data of each participant and will then administer the Life S-Can screener. Participants will be offered to complete the Life S-Can questionnaire again after 10 days to test for reproducibility (either by phone or in person, to be convened with the patient), based on the test-retest method.

An individual code will be used for each participant (structure: LS-XXX) when completing all questionnaires, which only the principal investigator and research dietitian will be able to trace to the individual. On all electronic databases used in this project, only the code will be used so no other user can identify the identity of the participant. This same code will be used to mark all biological samples (saliva, blood). All questionnaires will be on an electronic platform and completed electronically.

**2 Administration of validated questionnaires:** To validate the data obtained using the Life S-Can tool, it is essential to collect the same type of data using validated methods. The following validated and extensively used and published questionnaires will be administered for each of the specified domains: body composition (SARC-F, to determine sarcopenia); physical activity (IPAQ); fatigue (QLQ-30); diet and alcohol (a 143-item validated food frequency questionnaire, a semi-quantitative questionnaire which is repeatedly used in epidemiological studies in Spain, such as PREDIMED-Plus); smoking (adapted Spanish questionnaire from the National Statistics Institute); sleep (Pittsburgh Sleep Quality Index); and psychosocial distress (Perceived Stress Scale – stress; QLQ-30 and PHQ-9 – mental health and quality of life –; Multidimensional Scale of Perceived Social Support – social support –). The principle of data minimization established by the Reglamento General de Protección de Datos (Reglamento (UE) 679/2016 del Parlamento Europeo y del Consejo del 27 de abril de 2016), articles 5 & 89, will be taken into account, and thus only the strictly necessary data will be collected.

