**3. Obtain objective measurements:**

- **Body weight and height** will be measured by a research dietitian at the Clinical Trials Unit.
- **Physical activity**: Physical activity, sedentary behaviour and sleep quality will be measured using an accelerometer. All participants will be offered to wear an accelerometer for 7 to 10 days. Accelerometry is one of the most reliable techniques for recording and storing the amount and level of physical activity performed by each person and in a given period of time. An accelerometer will be provided to the participant and it will be explained how to use it, and it will have to be returned after 7-10 days. These accelerometers are owned by the NUTRECOR research group and do not imply any added cost for the research group or for the participant. In addition, the use of an accelerometer constitutes a non-invasive technique.
- **Skeletal muscle mass and fat mass** Skeletal muscle mass and fat mass will be determined by a technician from the Nuclear Medicine Imaging Unit using DXA if possible, or using the bioimpedance measurement technique. DXA analysis is of interest to measure skeletal muscle accurately (in this case, for the interest of determining sarcopenia); however, it implicates a small exposure to radiation, similar to that of an X-ray. For this reason, participants will be given the option to either opt out of this procedure and/or analyze body composition via bioimpedance (which is less accurate for muscle mass).
- **Muscle function**: Muscle function will be determined using grip hand strength and the 30-s chair test.
- **Stress** will be measured by cortisol levels in the saliva samples brought in by the patient. Briefly, the salivary samples brought in by the participant will be stored at –80ºC and assayed for cortisol using an enzyme-linked immunosorbent assay kit following the protocol specified by Salimetrics. Samples will be assayed in duplicate.
- **(optional) Blood sample extraction:** All participants will be offered the option to provide a blood sample, which will be centrifuged to obtain blood specimens and will be stored at -80ºC for future studies in this cohort. This will be completely optional and will not determine participant inclusion in the study.

Staff from the Clinical Trials Unit will aid in sample obtention, processing and storing (research technicians) of all biological samples.

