**Data integration and statistical analysis:** All data obtained using the questionnaires and the objective measurements will be integrated into a database. Any additional medical data needed will be obtained through medical records (prior consent by the participant). A data management plan following the FAIR principles will be established. Construct validity will be studied using the hypothetical latent structure, structural equation models and psychometric tests. Pearson correlation and Intraclass correlation and Cohen’s Kappa will be used to test the relative validity, reliability and reproducibility of the screener. Internal consistency of the screener will be analysed using Cronbach Alpha.

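### For domains referenced only by questionnaire, same-visit answering can raise the validity correlation, and the repeat Life S-Can that could partly show this is used only for reproducibility and follows disclosure of results

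*Protocol*

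**What the plan says.** **Visit 1.** Protocol section 7, Phase II, Workflow of the validation study, sets a single session of about an hour with this sequence of steps: "1) Administration of Life S-Can; 2) Administration of validated questionnaires; and 3) Obtain objective measurements of the patient". The Abstract gives the same order: "A dietitian will administer Life S-Can and then collect data using validated assessment methods".

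**References.** The paragraph on validated questionnaires explains that "it is essential to collect the same type of data using validated methods", and lists a self-report instrument for every domain. The paragraph on objective measurements adds references that do not depend on recall:
- measured weight and height, DXA or bioimpedance, grip strength and a chair test for body composition;
- an accelerometer: "Physical activity, sedentary behaviour and sleep quality will be measured using an accelerometer";
- salivary cortisol for stress.

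Nothing of this kind is listed for diet, alcohol, smoking, mental health or social support.

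**Repeat.** "Participants will be offered to complete the Life S-Can questionnaire again after 10 days to test for reproducibility". Aim A2.2 gives the interval as 7 to 10 days and the same purpose. The repeat is optional and may be done by phone or in person.

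**Analysis.** Pearson correlation, intraclass correlation and kappa "will be used to test the relative validity, reliability and reproducibility of the screener". The paragraph does not say which administration of Life S-Can is set against the references.

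**Disclosure.** In Phase III, Groups of intervention, control participants are given their screener results as part of the account of the baseline visit. Under Baseline visit, randomisation follows completion of that visit, and intervention participants receive appointments according to their score.

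**The concern.** Someone who has just answered the screener's items on diet, alcohol or smoking meets the same subject again minutes later in the reference questionnaire. Recall of the first answer, a wish to be consistent and the mood of that hour can enter both measures. Their errors are then positively correlated, and the correlation between the measures rises for a reason unrelated to the screener's validity. This comes from the respondent, so blinding the dietitian to the score would not remove it.

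Body composition, activity, sleep and stress have a reference that memory of an answer cannot affect. Three of the seven domains (diet, alcohol, smoking) and part of a fourth (psychosocial distress) do not. For them the same-visit questionnaire coefficient is the only relative-validity evidence described, although specific aim 2 sets out to validate individual domains. The diet and psychosocial scores also steer who is offered a dietitian or psychologist in Phase III.

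The protocol already collects a second Life S-Can away from that sitting, but does not use it for this purpose. By the time it is taken, at least the control group has been told its results. A participant who has seen a poor domain score may answer differently, or behave differently, by the repeat. That affects the test-retest estimate whether or not any same-visit carry-over exists.

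**Working it through.** **1. Inputs from the protocol.** One visit of about 1 h, screener before references; repeat at 7 to 10 days; target n = 100. The recruitment figure reproduces as 100 × 1.20 = 120, and a 20% loss from 120 leaves 96. The point does not rest on that figure. The protocol gives no expected validity coefficient, reliability or shared-error figure, so everything below rests on assumed ranges.

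**2. Model.** With reliabilities rel1 and rel2, true-score correlation r_T and error correlation e:

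observed r = r_T × sqrt(rel1 × rel2) + e × sqrt((1 − rel1)(1 − rel2)).

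The first term is the correlation that would be seen without shared error. The second is the same-sitting increment.

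**3. Increment, equal reliabilities**, so that it equals e × (1 − rel):

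| rel | e = 0.2 | e = 0.4 |
|---|---|---|
| 0.6 | 0.2 × 0.4 = 0.08 | 0.4 × 0.4 = 0.16 |
| 0.7 | 0.2 × 0.3 = 0.06 | 0.4 × 0.3 = 0.12 |
| 0.8 | 0.2 × 0.2 = 0.04 | 0.4 × 0.2 = 0.08 |

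If the correlation without shared error is 0.50, the observed value is therefore 0.54 to 0.66.

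**4. What 0.50 must mean.** If 0.50 were the true-score correlation, attenuation has to be included. Observed r is then 0.50 × rel + e × (1 − rel):
- rel 0.6: 0.30 + 0.08 = 0.38 to 0.30 + 0.16 = 0.46;
- rel 0.7: 0.35 + 0.06 = 0.41 to 0.35 + 0.12 = 0.47;
- rel 0.8: 0.40 + 0.04 = 0.44 to 0.40 + 0.08 = 0.48.

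All lie below 0.50. Shared error raises the observed coefficient relative to the same measures without it. Over these ranges it does not lift it above the true-score correlation.

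**5. Scale.** The Fisher 95% interval for r = 0.50 at n = 100 is 0.34 to 0.63. An increment of 0.04 to 0.16 runs from well inside that interval to slightly beyond its upper limit. Unlike sampling error, it does not shrink with n.

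**6. What the repeat could show.** In simulated trivariate normal data, I took the correlation of the repeat with the visit-1 reference as 0.4 or 0.5, the retest correlation as 0.7 or 0.8, and the same-visit correlation as higher by a set gap. The standard error of the difference between the two coefficients at n = 100 is 0.053 to 0.070. Power of a two-sided 5% test is Φ(gap/SE − 1.96); for example, Φ(0.10/0.069 − 1.96) is about 0.30.

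| gap in r | power, n = 100 | power, n = 80 |
|---|---|---|
| 0.05 | 11–15% | 9–13% |
| 0.10 | 30–46% | 25–39% |
| 0.15 | 59–80% | 50–72% |
| 0.20 | 85–97% | 76–92% |

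**7. True change alone.** If stability over the interval is 0.90 to 0.95, the correlation falls by r × (1 − stability): from 0.4 × 0.05 = 0.02 to 0.6 × 0.10 = 0.06. A gap of that size can arise with no carry-over at all.

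**The case against.** Answering both instruments on one day is a usual choice for concurrent validity, because delay mixes real change into the comparison. That stands, and the visit order should not be changed.

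Carry-over is also not shown. The screener is still to be written, with at most 25 questions, and the diet and alcohol reference has 143 items. A few remembered answers do not readily reproduce so many frequency responses, and identical smoking answers may simply be true. This stands too: upward is the plausible direction, but the effect may be small.

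A reader might infer that the repeat should replace the same-visit coefficient as the validity result. The protocol does not support that. The repeat is optional, may be by phone and follows completion of the references. A coefficient based on it therefore mixes true change, reactivity, mode and selective response, while habitual misreporting stays in both measures. It would exchange one bias for several.

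Finally, the choice of which administration enters which coefficient could be left to a statistical analysis plan, which is not at hand. That is fair for the extra correlation. It does not cover disclosure: when participants learn their results is protocol workflow, and no later analysis can undo a repeat taken after disclosure.

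**Conclusion.** The point holds in a limited form. For diet, alcohol, smoking, and the mental-health and social-support parts of psychosocial distress, the same-visit design can raise the observed validity correlation above its value without shared error. The increment is about 0.04 to 0.16 in r, if error correlations are 0.2 to 0.4 and reliabilities 0.6 to 0.8; the protocol supplies none of these. The repeat that could partly bound the increment is assigned only to reproducibility. As described, it comes after randomisation and after at least the control group has its results, which puts the test-retest estimate itself at risk.

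Three stronger readings might be inferred and are not supported:
- That the coefficients are shown to be inflated: the protocol contains no evidence of presence or size.
- That all relative validity is affected: body composition, activity, sleep and stress have references that recall cannot touch.
- That the reported correlations would exceed the true-score correlations: step 4 shows that they would not over the assumed ranges.

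**What to change.** 1. **Phase III, Groups of intervention and Baseline visit:** state that Life S-Can results are disclosed, in both groups, only after the 7 to 10 day repeat or, for those who decline it, once its window has closed.

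2. **Phase II, Data integration and statistical analysis:** for the domains named above, keep visit-1 Life S-Can against the visit-1 reference as the main concurrent-validity result. Beside it, as a sensitivity analysis in the same participants, report the repeat Life S-Can against the visit-1 reference, with a confidence interval for the difference. Read the two together with the test-retest intraclass correlation and the mode of the repeat (phone or in person), and name shared-session error as a limitation.

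**Cost.** The analysis needs a sentence or two and one more set of correlations on data already collected. The workflow change delays feedback by about 7 to 10 days; since intervention sessions are envisaged monthly, it should fit, but the investigators must confirm this. The second coefficient may be less favourable, absorbs true change and mode effects, does not remove stable misreporting, and is imprecise for gaps of 0.05 to 0.10 at n of about 100. A small gap therefore should not be read as proof that carry-over is absent.
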